# 2. COVID-19 CLINICAL PROFILE

Important published research studies on COVID-19 were selected to tabulate the data on symptoms (Table 1), timelines of the course of disease (Table 2), complications (Table 3) and co-morbidity (Table 4).

COVID-19 is an acute respiratory tract infection. Though the clinical phenotype is similar to influenza, the spread and severity of illness is much more in case of COVID-19. The overall mortality of COVID-19, albeit due to respiratory complications, seems to be several folds higher than that of influenza. And unlike influenza, there is no vaccine or specific drugs to kill the virus.

Viral RNA levels have been demonstrated from upper respiratory and lung specimens. In over 90% cases, the viral RNA tests on nasopharyngeal swabs was found to be repeatedly negative at about 10 days after the onset of symptoms but the viral shedding may continue well beyond clinical recovery; median duration 20 days (range of 8 to 37 days) (9,10). In mild infections, the virus may not be detected especially if the viral RNA level in respiratory specimen is less than 106 copies/mL. Some recent studies have also shown prolonged virus shedding in stool samples.

The incubation time of COVID-19 is about 5-7 days and the infectivity is often high much before the onset of symptomatic illness (11). The infection remains asymptomatic in a substantial proportion of community and a predominant proportion of symptomatic cases will suffer from mild to moderate cases. However, asymptomatic individuals may show abnormalities in the lungs on computed tomography (CT) scans (12). It is estimated that less than 20 % cases will rapidly progress to severe stage and develop life threatening lung and systemic complications requiring critical care and often life support systems like ventilators. The overall mortality rate is about 2-3%. According to the WHO, the recovery time appears to be around two weeks for mild infections and three to six weeks for severe disease.

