**Table 2: COVID-19 TIMELINES OF THE COURSE OF DISEASE (LITERATURE REVIEW#):**

| **Study** | **Wang et al.^1^** | **Li et al.^2^** | **Huang et al.^3^** | **Zhou et al.^4^** |
| --- | --- | --- | --- | --- |
| **Site** | China | China | China | China |
| **Study type** | Retrospective  Observational  Single center | Prospective  Observational  Multicenter | Prospective  Observational  Single center | Retrospective  Observational  Multi center |
| **Nature of Site** | Hospital | Hospital | Hospital | Hospital |
| **Sample size** | 138 | 425 | 41 | 191 |
| **Time to symptoms- Median days (IQR)** | | | | |
| **Fever** | -- | -- | -- | 1 (1-1) |
| **Cough** | -- | -- | -- | 1 (1-3) |
| **Dyspnoea** | 5 (1-10) | -- | 8 (5-13) | 7 (4-9) |
| **1^st^ Hospital visit** |  | 4.6 (95%CI 4.1-5.1) | 8 (5-13) | -- |
| **Hospital admission** | 7 (4-8) | 9.1 (95%CI 8.6-9.7) | 7 (4-8) | -- |
| **Time to complications- Median days (IQR)** | | | | |
| **ICU admission** | -- | -- | 10.5 (8-17) | 12 (8-15) |
| **Mechanical Ventilation** | -- | -- | 10.5 (7-14) | 14.5 (12-19) |
| **ARDS** | 8 (6-12) | -- | 9 (8-14) | 12 (8-15) |
| **Sepsis/ Shock** | -- | -- | -- | 9 (7-13) |
| **Acute Cardiac injury** | -- | -- | -- | 15 (10-17) |
| **Acute Kidney injury** | -- | -- | -- | 15 (13-19.5) |
| **Time to outcome- Median days (IQR)** | | | | |
| **Discharge** | -- | -- | -- | 22 (18-25) |
| **Death** | -- | -- | -- | 18.5 (15-22) |
| **Recovery** | 10 (7-14) | -- | -- | -- |
| **Others** | -- | -- | -- | Viral shedding:  20 (17-24)  Severe disease:  19 (17-22)  Critical disease:  24 (22-30) |

ARDS: Acute respiratory distress syndrome. IQR: Interquartile range, CI: Confidence interval.

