# 3. RATIONALE FOR PROPOSED STUDY

The absence of specific drug treatment and lack of vaccine is a critical gap in the knowledge of COVID-19 pandemic (38). And in this regard it is important to refer to a seminal paper published on the ‘responsibility and accountability of conducting standard research including randomized clinical drug trials by the medical community’ in times of epidemics, and the authors have used the recent Ebola virus epidemic in Africa to highlight their contention (39).

The Ministry of AYUSH, GOI has recommended the self-care guidelines for preventive health measures and boosting immunity with special reference to respiratory health based on Ayurvedic literature and scientific publications. However, this advisory does not claim to be treatment for COVID-19. The role of Ayurveda Rasayana as an immunomodulator is well known and should be investigated in COVID-19 (40). In this protocol, we describe the rationale for using three Ayurveda herbal formulations individually to treat COVID-19 as an add-on/adjunct therapy to standard of care. The three Ayurveda formulations are AYUSH-64, Sanshamani Vati Plus and Yashtimadhu. In India the guidelines issues by the Ministry of Health and Family Welfare are generally followed as standard of care (See above, Section 2.6 (20). It is difficult if not impossible to expect a uniform nature of standard of care in the study site hospitals in this study.

Patients suffering from symptomatic Mild to Moderate COVID-19 will be selected for this study. By ’Mild to Moderate’ it would essentially mean that patients do not require any of the emergency measures that are advocated for severe and life-threatening cases of COVID-19. The latter would include complications of progressive lung disease, septicemia, shock and other complications (see Table 3). The mild to moderate cases of COVID-19 will belong to the categories of ‘Mild’ and ‘Pneumonia’ as described by WHO (See WHO Table on Syndromes associated with COVID-19 shown in Section 2.6 above). Mere need for supplement oxygen using non-invasive means will not negate the classification of mild to moderate COVID-19.

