# CONSENT, SELECTION, SCREENING, and ENROLLMENT

Study patients will be served on first come first serve basis as per the protocol.

Consenting and eligible patients will be enrolled as soon as possible in a COCID-19 management facility and the study intervention begun. It is important that symptomatic patients suspected for COVID-19 on clinical grounds are quickly evaluated for eligibility. It is important to enroll the patient as close to the onset of symptoms as possible. As described above, this study is dealing with patients of COVID who are ‘non-emergent’ which means mild and moderate disease (pneumonia) which does not require emergency or critical care (see section on inclusion and exclusion criteria).

An ‘Patient Information Sheet’ (Appendix F) in the language understood by the patient will be provided to each patient for study and discussion prior to enrollment. The information fact sheet will describe the overall design of the study and the rationale, benefit and side effect profile of the study drug interventions, and other aspects of the study.

Patients will be selected from the outpatient or inpatient facility in COVID-19 medical centres/ hospitals. The study will be explained to the volunteer patients and those willing to sign the informed consent (Appendix G) will be screened for eligibility as per the inclusion and exclusion criteria in the protocol.

Though it will be preferable to enrol patients with diagnosis confirmed by a positive RT-PCR assay using a nasal or throat swab in a standardized procedure, a patient with a clinical diagnosis of COVID- 19 as described below will be eligible.

Eligible patients will be enrolled using a simple randomization table (provided to the investigator) in a block of 20 patients each to either of the two study arms - SOC plus Ayurveda drug or SOC. As the target sample size is 70 patients in each arm, the first block of randomized allocation will be of 10. The study randomization will be carried out by the investigator.

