# 10. PATIENT POPULATION

The patients will be largely drawn from COVID-19 clinics and outpatients in various medical colleges and hospitals. All patients will be admitted in the hospital for standard care and those willing to participate in the study will be screened and enrolled as described above. Only patients with mild to moderately severe symptoms will be selected as described above. If the patients progress to a severe stage of illness as described below, they will be withdrawn from the study but the investigator will be encouraged to follow the patient ill study completion at week 12 and during this period record the hospital management, course of illness , final outcome and post recovery health status as described in this protocol.

- 1. Inclusion Criteria:

1. Typical Clinical presentation of acute onset febrile illness with cough and a RT_PCR based laboratory confirmation test for COVID-19
2. Patients with either sex, 21to 69years age
3. Patients with Mild to Moderate COVID-19 as described below
4. All patients must agree not to share medication
5. Patients willing to participate and sign an informed consent
   Note: The criteria for mild to moderate COVID-19 are based on the WHO recommendations (See Section 2.5 above with WHO Table on clinical syndromes of COVID-19 and include Mild disease and Uncomplicated Pneumonia but not severe disease which requires any form of intensive care such as invasive techniques for supplemental oxygen or ventilation and life support systems, and absence of any life threatening complications (such as severe respiratory failure, adult respiratory distress syndrome, septicaemia shock and other complications shown in Table 3 above)
   1. Exclusion Criteria

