**Criteria of ‘Clinical Recovery’**:

1. Normal body temperature (≤36.6°C axilla or ≤37.2 °C oral)
2. Absence of cough or mild cough (infrequent, short episodic, non-wheezy, relieved by minimal or no medication, not interfering with routine speech and not related to lying in bed, mild sore throat or nasal congestion)
3. Absence of breathlessness on routine daily self-care chore or respiratory rate less than 30 breaths per minute without supplemental oxygen
4. Absence of any other symptom/sign attributed to COVID-19 illness
5. Normalization of SpO2 by standard peripheral oximetry device (above 95 percent)
6. Recovery should be sustained for at least 48 hours under physician observation
7. Assessed by physician blinded to treatment allocation
8. All of the above criteria ought to be fulfilled

Note: Clinical recovery would be deemed from the first day of satisfying the above criteria

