**DATE OF INFORMED CONSENT__________LANGUAGE OF INFORMED CONSENT ________**

**STUDY GROUP:** □ **STANDARD OF CARE** □**AYURVEDA**

Name of Drugs_____________________________________________________

ADMISSION DATE TO HOSPITAL___________________________________

STATUS OF DISEASE ON ADMISSION: □ MILD □MODERATE

Note: Please check ‘INCUSION and EXCLUSION CRITERIA’ on page 4

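### Entry criteria and the clinical-recovery endpoint overlap at the mild end: nothing bars randomising a patient who already meets the recovery criteria, which would dilute both primary outcomes.

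*Combined protocol and SAP*

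**What the plan says.** **Entry.** Inclusion item 1 in Section 10 reads "Typical Clinical presentation of acute onset febrile illness with cough and a RT_PCR based laboratory confirmation test for COVID-19". The synopsis and the case record form (CRF) checklist in Appendix H carry the same item. The narrative adds that symptoms are expected. Section 3 says "Patients suffering from symptomatic Mild to Moderate COVID-19 will be selected for this study", and the opening of Section 10 says "Only patients with mild to moderately severe symptoms will be selected as described above". On timing, the enrolment section says only "It is important to enroll the patient as close to the onset of symptoms as possible" and gives no number of days. The CRF cover page asks for "STATUS OF DISEASE ON ADMISSION", which is not the status at randomisation.

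**Endpoint.** Section 11.1 counts recovery time from the day of randomisation. Items 1 to 5 of the recovery criteria cover temperature, cough, breathing, other COVID-19 symptoms or signs, and SpO2. Items 6 to 8 require 48 hours of sustained recovery under observation, a blinded assessor, and all criteria together. The note below them says "Clinical recovery would be deemed from the first day of satisfying the above criteria".

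**The concern.** Both primary outcomes assume that each patient has something to recover from at randomisation. The listed criteria do not secure this. Item 1 describes how the illness presented and requires a confirmatory PCR. Neither shows that the patient is still ill on the day of allocation, and Section 2 notes that "viral shedding may continue well beyond clinical recovery; median duration 20 days".

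A patient who already meets the recovery criteria cannot show a drug effect on time to recovery or on the proportion recovered. Such patients contribute the same result to both arms, pull the two means and the two proportions together, and add spread to the recovery times. With a convenience sample of 70 per arm, a null result could then partly reflect who was enrolled.

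**Working it through.** **Step 1: compare entry with recovery.**

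| Feature at randomisation | Eligible? | Recovered under items 1 to 5? |
|---|---|---|
| Afebrile, after a febrile onset | Yes; no listed criterion requires current fever | Yes, item 1 |
| Mild cough, mild sore throat or nasal congestion | Yes; the WHO description of mild disease in Section 2 includes these symptoms | Yes, item 2 tolerates them |
| No breathlessness, respiratory rate below 30 | Yes, not severe | Yes, item 3 |
| No other COVID-19 symptom or sign | Yes | Yes, item 4 |
| SpO2 above 95% | Yes, not severe | Yes, item 5 |
| PCR positive | Yes | Not part of the definition |

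One patient can satisfy both columns. The symptom sentences in Sections 3 and 10 do not separate them, because the residual symptoms allowed after recovery are also symptoms of mild disease.

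**Step 2: effect on the outcomes.** The plan states no effect size, SD or power, so it has no figure of its own to reproduce beyond 70 + 70 = 140. The following is an illustration.

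- From the documents: 70 per arm (Section 17.1); two-sided 0.05 and ANOVA for mean time (Section 17.2), which with two arms is the t-test.
- Assumed: among patients still ill, mean recovery of 10 days (control) and 8 days (drug), SD 5; a share f of each arm already recovered and scoring 0.

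Difference in means = (1 − f) × 2. Variance in an arm with mean μ = (1 − f) × 25 + f(1 − f) × μ².

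For f = 0.2:
- Control: 0.8 × 25 + 0.16 × 100 = 36.00.
- Drug: 0.8 × 25 + 0.16 × 64 = 30.24.
- Average 33.12, so SD 5.76. Difference 1.6, standardised 1.6 / 5.76 = 0.28.
- Noncentrality 0.278 × √(70/2) = 1.645; power from the noncentral t is 37%.

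| f | Difference (days) | SD | Standardised | Power |
|---|---|---|---|---|
| 0 | 2.0 | 5.00 | 0.40 | 65% |
| 10% | 1.8 | 5.47 | 0.33 | 49% |
| 20% | 1.6 | 5.76 | 0.28 | 37% |
| 30% | 1.4 | 5.89 | 0.24 | 29% |

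**Step 3: sensitivity.** Table 2 gives one recovery time as a median of 10 days, IQR 7 to 14. This implies an SD of about 7 / 1.349 = 5.19. With that SD and the same 2-day difference, power (normal approximation) is 63%, 47%, 36% and 28% for f = 0, 10, 20 and 30%.

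For the proportion recovered, each arm becomes f + (1 − f)p. With an assumed 70% versus 90%, the difference falls from 20 points to 18, 16 and 14, and power from 85% to 80%, 74% and 67%.

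**The case against.** **The plan does say that patients are symptomatic.** A reader might infer from inclusion item 1 alone that the trial ignores whether the patient is still ill. Sections 3 and 10 contradict that reading. What stands is narrower: the requirement is not put into a criterion checked at randomisation, and it overlaps with the recovery definition.

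**Already-recovered entrants need not be common.** A reader might infer that they are likely, since Table 2 puts admission at a median of 7 days, or about 9 days, from onset, and PCR can stay positive after recovery. The documents do not support that. The Section 2 sentence on shedding begins by saying that over 90% of cases were repeatedly PCR negative at about 10 days. Table 2 places dyspnoea at medians of 5 to 8 days and ARDS at 8 to 12, so these are also the days on which hospital patients worsen. Section 8 expects most discharges 5 to 15 days after hospitalisation. Item 4 also rules out any patient with, for example, residual fatigue or loss of smell attributed to COVID-19. The share is unknown.

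**Day 0 is not certain.** The 48-hour rule is itself one of the criteria, so a literal reading dates recovery about two days later. That moves every patient's recovery by the same amount, so the difference, the spread and the power loss are unchanged.

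**The trial is exploratory and expressly unpowered.** True, but the synopsis still calls 70 per arm enough for meaningful conclusions at p < 0.05, and the dilution is avoidable.

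**A duration rule does exist.** Exclusion item 5 of the CRF checklist concerns fever lasting more than 72 hours. It is not a limit on overall illness duration, and it removes patients with persisting fever, not recovered ones. It is absent from Section 10 and the synopsis.

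**Conclusion.** The concern holds as an overlap between mild symptomatic disease and clinical recovery. No listed criterion in Section 10, the synopsis or the CRF checklist prevents a patient who meets recovery items 1 to 5 from being randomised and counted as recovered at once.

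The consequence is dilution of both primary outcomes. A reader might infer a bias for or against the drug. That does not follow, because randomisation is expected to spread such patients equally over the arms.

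The size cannot be fixed from the documents. The loss from about 65% power to between 49% and 29% rests on an assumed share of 10% to 30% and on assumed means and SD. If the share is near zero, the loss is near zero. The case for acting is that the gap is real and closing it is cheap, not that a large loss has been shown.

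**What to change.** Add one inclusion criterion to Section 10, the synopsis and the CRF checklist: on the day of randomisation, at least one of clinical-recovery items 1 to 5 is not met. Record which item, with the date. The symptom assessment, vital signs and pulse oximetry scheduled at Visit 1 already supply the data, so the cost is one amendment and one CRF entry. The downside is that a few nearly well patients are screened out and recruitment is slightly slower.

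A maximum time from onset is not needed for this purpose. A cap of 7 days, for instance, would sit at one of the median admission times in Table 2 and could exclude about half of patients.

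Separately, reconcile the CRF exclusion on fever beyond 72 hours with Section 10, which does not contain it, so that all sites screen against one list.

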# 11. EFFECTIVENSS MEASURES

**11.1 Primary Efficacy:**

1. Mean time (days) for clinical recovery (Day of randomization to the Day of clinical recovery (see criteria below] [Time Frame: up to 28 days]
2. Proportion of patients showing ‘clinical recovery’

**Criteria of ‘Clinical Recovery’**:

1. Normal body temperature (≤36.6°C axilla or ≤37.2 °C oral)
2. Absence of cough or mild cough (infrequent, short episodic, non-wheezy, relieved by minimal or no medication, not interfering with routine speech and not related to lying in bed, mild sore throat or nasal congestion)
3. Absence of breathlessness on routine daily self-care chore or respiratory rate less than 30 breaths per minute without supplemental oxygen
4. Absence of any other symptom/sign attributed to COVID-19 illness
5. Normalization of SpO2 by standard peripheral oximetry device (above 95 percent)
6. Recovery should be sustained for at least 48 hours under physician observation
7. Assessed by physician blinded to treatment allocation
8. All of the above criteria ought to be fulfilled

Note: Clinical recovery would be deemed from the first day of satisfying the above criteria

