**i. Eligibility:**

1. **Inclusion Criteria:**
2. Typical clinical presentation of acute onset febrile illness with cough and a RT_PCR based laboratory confirmation test for COVID-19
3. Patients with either sex, 18 to 75 years age
4. Patients with mild to moderate patients
5. All patients must agree not to share medication
6. Patients willing to participate and sign an informed consent
7. Exclusion Criteria:
8. Patients suffering from severe COVID-19 Disease as judged by a physician and fulfilling at least two of the following three criteria* (i) Respiratory distress at room ambience (≥30 breaths per min) (ii) Oxygen saturation at rest ≤93% (peripheral digital arterial oxymetry) and requiring oxygen support for over one hour to normalize (iii) Any of the known COVID-19 complications and emergency procedures which may require shift/admission in intensive care unit such as respiratory failure, adult respiratory distress syndrome, requirement of oxygen support for over 1 hour, requirement of mechanical ventilation, septic shock, or severe non-respiratory organ dysfunction or failure.
   (Adapted and modified from the reference: Yang Liu et al. Lancet Infect Dis 2020, 2020 https://doi.org/10.1016/ S1473-3099(20)30232-2)
9. Chronic, Severe, Unstable, Uncontrolled co-existent medical illness such as Diabetes, Hypertension, Cardiac disorders, liver, kidney disorders and lung disorders or other disease of concern which may put the patient at increased risk during the study
10. History of immunosuppression: solid organ or bone marrow transplant, use of immunosuppressive antimetabolic and biologic agents, intrinsic immunodeficiencies, HIV infection.
11. Active cancer diagnosis, on palliative treatment or requiring current therapy with antimetabolic agents, immunotherapy or radiotherapy.
12. Patients on parenteral nutrition
13. Patients with known sensitivity or contraindication to any of the ingredients of study medication
14. History of bleeding haemorrhoids, haemoptysis, acid peptic diseases, ulcers and pulmonary diseases (tuberculosis, asthma, etc.)
15. Patients who are likely to worsen or planed ICU admission or ventilator support due to any reason
16. Pregnancy and lactation
17. Participation in a drug interventional clinical drug trial of any nature in the three month period preceding onset of COVID-19
18. Participation in any other clinical trial of an experimental agent treatment for COVID-19

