6. Patients suffering from severe COVID-19 Disease as described above in Section 10.1 and judged by a physician; further guidance can be taken to exclude patient in a clinical context of progressive respiratory dysfunction and failure from the following criteria (i) Respiratory distress at room ambience (≥30 breaths per min) (ii) Oxygen saturation at rest ≤93% (peripheral digital arterial oxymetry) and requiring oxygen support for over one hour to normalize (iii) Any of the known COVID-19 complications and emergency procedures which may require shift/admission in intensive care unit such as respiratory failure, adult respiratory distress syndrome, requirement of oxygen support for over 1 hour, requirement of mechanical ventilation, septic shock, or severe non-respiratory organ dysfunction or failure.(62)
   (Adapted and modified from the reference: Yang Liu et al.Lancet Infect Dis 2020 , March 19, 2020 https://doi.org/10.1016/ S1473-3099(20)30232-2)
7. Chronic, Severe, Unstable, Uncontrolled co-existent medical illness such as Diabetes, Hypertension, Cardiac disorders, liver, kidney disorders and lung disorders or other disease of concern which may put the patient at increased risk during the study
8. History of immunosuppression: solid organ or bone marrow transplant, use of immunosuppressive antimetabolic and biologic agents, intrinsic immunodeficiencies, HIV infection.
9. Active cancer diagnosis, on palliative treatment or requiring current therapy with antimetabolic agents, immunotherapy or radiotherapy.
10. Patients on parenteral nutrition
11. Patients with known sensitivity or contraindication to any of the ingredients of study medication
12. History of bleeding haemorrhoids, haemoptysis, acid peptic diseases, ulcers and pulmonary diseases (tuberculosis, asthma, etc)
13. Patients who are likely to worsen or planed ICU admission or ventilator support due to any reason
14. Pregnancy and lactation
15. Participation in a drug interventional clinical drug trial of any nature in the three-month period preceding onset of COVID-19
16. Participation in any other clinical trial of an experimental agent treatment for COVID-19
17. Patients on any kind of Ayurveda treatment or any other alternative and complementary medicinal systems such as Homeopathy, Unani, Siddha and in particular requiring oral therapy of any kind
18. Patients receiving any other test drug, apart from SOC.

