**11.2 Secondary Efficacy:**

1) Rate of patients with negative SARS-CoV-2 on nasal or throat swab in a 2-day continuous real time RT-PCR test beginning from ‘first day of clinical recovery’ (see above) or ‘Day 10 after onset of symptoms depending on whichever of the two time points is first achieved

2) Timelines (days counted from onset of illness) - normal body temperature <37◦C, absence or minimal cough (see ‘clinical recovery’ for the definition), absence of dyspnoea (respiration rate 24/minute or less on room air), onset of clinical pneumonia, pneumonia diagnosed on chest X-Ray or CT scan, time to supplemental oxygen, admit in intensive care unit, mechanical ventilation (non-invasive), mechanical ventilation (invasive), steroid use, respiratory failure, adult respiratory distress syndrome, cytokine storm syndrome, secondary infection, shock, septicaemia shock, hospital discharge, death, negative nose or throat swab confirmatory test, all-cause mortality (Time Frame: up to 28 days).

Note: In case of symptoms, the absence on improvement should be sustained for at least 72 hours or live hospital discharge, whichever comes first.

3) Proportion OF patients developing an event that reflects clinical or otherwise improvement of worsening (the events are similar to those listed under Timelines, see above)

4) Improvement on pulmonary function tests using simple ‘home expiratory spirometer’ device and peripheral pulse oximetry

5) Improvement in selected laboratory parameters: blood haemoglobin, differential and total leukocyte counts, liver enzymes, renal functions, acute phase reactants, serum IL-6 and other selected cytokines, serum muscle enzymes (CK, CPK), serum ferritin, serum d-Dimer, anti-oxidant markers, serum BNP (cardiac function)

6) Serological Protective Antibody Assay (IgM and IgG)

7) Radiological Improvement on digital chest Xray and HRCT chest

8) Drug related: side effects and toxicity, and tolerability

9) Health status: WHO QOL (Appendix M) brief, health related behaviour habit and fitness questionnaire based on visual analogue scale (See Appendix N)

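### The breathing item of 'clinical recovery' can be met by a patient who is still breathless, and its rate limit conflicts with the dyspnoea definition in Section 11.2

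*Combined protocol and SAP*

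**What the plan says.** Section 11.1 names two primary measures: time from randomisation to clinical recovery, with a window of up to 28 days, and the proportion who recover. Both rest on one list of criteria, which closes with "All of the above criteria ought to be fulfilled". Item 3 is the breathing item: "Absence of breathlessness on routine daily self-care chore or respiratory rate less than 30 breaths per minute without supplemental oxygen". Synopsis section j uses the same words.

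Three neighbouring rules bear on it.

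- **The other recovery items.** Item 4 requires "Absence of any other symptom/sign attributed to COVID-19 illness" and item 5 "Normalization of SpO2 by standard peripheral oximetry device (above 95 percent". The rest cover temperature, cough, a 48-hour sustained period and a blinded assessor.
- **Severity at entry.** The first exclusion criterion in Section 10 lists "Respiratory distress at room ambience (≥30 breaths per min" as guidance on severe disease. Synopsis section i and the checklist in Appendix H apply it under a rule of "fulfilling at least two of the following three criteria".
- **The secondary timelines.** Section 11.2, item 2, gives "absence of dyspnoea (respiration rate 24/minute or less on room air", with a note for symptoms that "the absence on improvement should be sustained for at least 72 hours or live hospital discharge, whichever comes first". The parallel item in the synopsis gives no rate.

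**The concern.** An endpoint item should separate patients who have recovered from those who have not. Here the second limb is enough by itself, and it uses the complement of a severity marker. A patient can therefore satisfy the breathing item while the symptom it names is still present. The protocol also holds a second, tighter definition of the same thing in Section 11.2.

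Both primary measures use this list. If breathlessness is the last feature to clear, the recovery date is set too early, and an effect of the study drug on breathing cannot show in the primary result. The primary and secondary outcomes can also give opposite answers for the same patient on the same day. If the reading of item 3 is left until the data are in hand, the choice will be made in an open-label trial after the fact.

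**Working it through.** The plan states no figure to reproduce: 140 is 2 × 70, a convenience sample (Section 17.1). The check is therefore mainly one of logic.

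**Step 1. What item 3 passes.** The oxygen condition is taken to belong to the rate limb.

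| Breathless on self-care | Rate ≥30 | On oxygen | Item 3 with 'or' | Item 3 with 'and' |
|---|---|---|---|---|
| no | no | no | pass | pass |
| no | no | yes | pass | fail |
| no | yes | no | pass | fail |
| no | yes | yes | pass | fail |
| **yes** | **no** | **no** | **pass** | **fail** |
| yes | no | yes | fail | fail |
| yes | yes | no | fail | fail |
| yes | yes | yes | fail | fail |

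As written, item 3 fails only a patient who is breathless and also has a rate of 30 or more or is on oxygen. If the oxygen condition is read as applying to both limbs, the rows with oxygen change but the bold row does not.

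**Step 2. Does another item catch the bold row?** Item 4 is limited to other symptoms, and breathlessness already has its own item. Item 5 measures saturation only. The all-criteria rule does not help, because item 3 is already satisfied.

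**Step 3. How close is the rate limb to the entry condition?** Below 30 is the exact complement of the ≥30 severity marker. Section 3 confines entry to the WHO mild and pneumonia categories, and Section 2 places a rate above 30 in severe pneumonia. After randomisation, Sections 9 and 14 provide for withdrawal on progression to severe disease, and Section 9 also for persistent oxygen need. Two routes let a patient enter without meeting the limb: an isolated rate of 30 or more, which does not exclude automatically, and non-invasive oxygen, which Section 3 says does not by itself rule out mild to moderate disease.

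**Step 4. The two definitions side by side, on room air.**

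| Rate per minute | Item 3, Section 11.1 | Dyspnoea, Section 11.2 |
|---|---|---|
| 24 or less | pass | absent |
| 25 to 29 | pass | not resolved |
| 30 or more | pass only if not breathless | not resolved |

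Temperature conflicts in both directions. Section 11.1 uses ≤36.6°C axilla or ≤37.2°C oral, and Section 11.2 uses <37°C with no site. A reading of 37.1°C oral is normal only in the first, and 36.8°C axilla only in the second.

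**Step 5. How many patients?** Number misdated = 140 × d × q, where d is the share with dyspnoea and q the share of those whose breathlessness outlasts all other items. Table 1 of Section 2 gives d from 19% to 56.5%. The documents do not give q, so it is taken over its full range.

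- d = 0.19: 140 × 0.19 = 26.6, so 0 to 27 patients as q runs from 0 to 1.
- d = 0.565: 140 × 0.565 = 79.1, so 0 to 79 patients.

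**The case against.** The strongest reply is that the flaw lies in one component of a demanding composite. A wrongly dated patient must be afebrile, have no more than mild cough, have no other COVID-19 symptom, saturate above 95% and hold this for 48 hours before a blinded physician. Entry requires fever with cough, so items 1 and 2 probably set many recovery dates. Section 11.2 also analyses dyspnoea, spirometry and oximetry separately. The trial calls itself exploratory. All of this stands, and it limits the size of the problem. It does not change what item 3 passes.

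A reader might go further than the documents allow in five ways.

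- **That nearly all patients already meet item 3 at randomisation.** No baseline rate distribution is given, and the two routes in step 3 remain open. Closeness to the entry condition is an inference from eligibility. Patients are certainly not recovered overall at entry.
- **That 27 to 79 patients will be misdated.** Those figures set q = 1 and borrow d from hospital cohorts not limited to mild or moderate disease. The Indian series has 21 patients, so its 19% is about 4 people.
- **That the composite ignores the main respiratory symptom.** In every Table 1 series reporting both, cough is more common than dyspnoea (59 v 31, 68 v 19, 79 v 56.5, 57 v 19), and cough has its own item.
- **That the result is biased toward the study drug.** The loose item applies to both arms under blinded assessment, and nothing in the documents shows a direction.
- **That 48 hours against 72 hours is an error.** A composite and single-symptom timelines may use different sustained periods.

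The sponsor may have meant both limbs to apply, but the same conjunction is printed twice and nothing corrects it.

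**Conclusion.** The concern holds for the breathing item. Under its printed wording a patient who is breathless on self-care passes with a rate below 30 off oxygen, and no other item clearly stops this. The item conflicts with Section 11.2 for any patient on room air at 25 to 29 breaths per minute.

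The number affected cannot be derived from the documents. It is bounded above by 27 to 79 of 140, if the trial's share with dyspnoea falls in the Table 1 range, and is probably well below that because the other items must all be met first. The expected consequence is that some recovery dates are too early, the proportion recovered is somewhat too high, and an effect on breathing is harder to see. Because this is a rule of the primary endpoint, it should be settled before analysis even in an exploratory trial.

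**What to change.** In Section 11.1 and synopsis section j, join the two limbs of item 3 with 'and', so that absence of breathlessness and the rate limit off oxygen are both required. Reconcile the limit of 30 with the 24 per minute on room air in Section 11.2, so that one dyspnoea definition serves both outcomes, and state it in the synopsis secondary outcome too. Both edits are needed: changing the number while keeping 'or' would still pass a breathless patient with a low rate.

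Two alignments belong with this. The completion form (Appendix K) offers only mild or absent for breathlessness and should say which counts as recovered. The temperature cut-offs in Sections 11.1 and 11.2 should be reconciled, with the measurement site named.

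The cost is mainly wording, with somewhat later recovery dates. Data capture is nearly sufficient: the daily sheet in Appendix J records dyspnoea and respiratory rate, but only for inpatients and to day 20, while the window is 28 days. The post-discharge app in Section 19.3 asks about breathlessness but not rate. Section 8 expects most discharges within 5 to 15 days, so the gap concerns late recoveries; the plan should say how rate is obtained for them.
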